## Abstract

**Background:**

Women with a low socioeconomic status often have a vulnerable health status due to an accumulation of health-deteriorating factors such as poor lifestyle behaviors, including inadequate nutrition, mental stressors, and impaired health literacy and agency, which puts them at an unnecessary high risk of adverse pregnancy outcomes. Adequately preparing for pregnancy through preconception care (PCC) uptake and lifestyle improvement can improve these outcomes. We hypothesize that *nudging* is a successful way of encouraging engagement in PCC. A nudge is a behavioral intervention that changes choice behavior through influencing incentives. The mobile health (mHealth) app–based loyalty program *Pregnant Faster* aims to reward women in an ethically justified way and nudges to engage in pregnancy preparation by visiting a PCC consultation.

**Objective:**

Here, we first describe the process of the cocreation of the mHealth app *Pregnant Faster* that aims to increase engagement in pregnancy preparation by women with a vulnerable health status. Second, we describe the cohort study design to assess the feasibility of *Pregnant Faster*.

**Methods:**

The content of the app is based on the eHealth lifestyle coaching program Smarter Pregnancy, which has proven to be effective in ameliorating preconceptional lifestyle behaviors (folic acid, vegetables, fruits, smoking, and alcohol) and an interview study pertaining to the preferences of the target group with regard to an mHealth app stimulating PCC uptake. For moral guidance on the design, an ethical framework was developed based on the bioethical principles of Beauchamp and Childress. The app was further developed through iterative cocreation with the target group and health care providers. For 4 weeks, participants will engage with *Pregnant Faster*, during which opportunities will arise to earn *coins* such as reading informative blogs and registering for a PCC consultation. Coins can be spent on small fun rewards, such as folic acid, fruits, and mascara. *Pregnant Faster*’s feasibility will be tested in a study including 40 women aged 18 to 45 years, who are preconceptional or <8 weeks pregnant, with a low educational level, and living in a deprived neighborhood. The latter 2 factors will serve as a proxy of a low socioeconomic status. Recruitment will take place through flyers, social media, and health care practices. After finalization, participants will evaluate the app through the “mHealth App Usability Questionnaire” and additional interviews or questionnaires.

**Results:**

Results are expected to be published by December 2023.

**Conclusions:**

*Pregnant Faster* has been designed through iterative cocreation with the target group and health care professionals. With the designed study, we will test *Pregnant Faster*’s feasibility. If overall user satisfaction and PCC uptake is achieved, the app will be further developed and the cohort will be continued with an additional 400 inclusions to establish effectiveness.

**International Registered Report Identifier (IRRID):**

DERR1-10.2196/45293

## Introduction

### Background

Although decreasing, perinatal morbidity and mortality rates are still relatively high in the Netherlands, especially among women who live in deprived neighborhoods and have a low socioeconomic status (SES) [1-3]. These women, who represent up to 45% of the total population in the 4 largest cities in the Netherlands [4], are more likely to have adverse pregnancy outcomes based on the accumulation of health-deteriorating risk factors such as poor lifestyle behaviors (eg, smoking, alcohol consumption, and sedentary lifestyle), inadequate nutrition (consumption of unhealthy food or insufficient intake of healthy food), mental stressors, and impaired health literacy and agency [5-7]. These risk factors, some of which are modifiable, can detrimentally influence the pregnancy course and outcome in the periconceptional phase comprising the preconceptional period of gametogenesis and the first 3 months of embryogenesis and placentation [8]. Complications that occur later in pregnancy are also more common among these women, such as preeclampsia and low birthweight [9-11]. These outcomes result in increased perinatal morbidity and mortality that has its origin in the periconceptional period. Furthermore, there is an increasing body of evidence showing that these pregnancy complications increase the risk of noncommunicable diseases in mothers and their infants during their life course, such as obesity, cardiovascular disease, and diabetes [12,13]. Therefore, we categorized these women with a low SES as women with a vulnerable health status. In short, the vulnerable health status of women with a low SES leads to an increased risk of adverse pregnancy outcomes, which in turn leads to deterioration of the offspring’s health, causing them to have a vulnerable health status as well, impacting the health and lives of generations (Figure 1).

**Figure 1 figure1:**
[figure not shown]
Generational impact of the vulnerable health status in women with a low socioeconomic status.

Most clinical manifestations of adverse pregnancy outcomes, such as hypertension or fetal growth restriction, are terminal features of a cascade of events that originate in the periconceptional period (ie, the 14 weeks before conception up to the first 10 weeks of pregnancy) [14]. During this period, on which the focus is limited in research as well as in clinical practice, modifiable poor lifestyle behaviors are known to be common risk factors for subfertility and adverse pregnancy course and outcomes [15-17]. For example, ≥80% of women who are contemplating pregnancy have at least one modifiable behavior associated with adverse pregnancy outcomes, such as not taking folic acid supplements, low vegetable and fruit intake, and smoking [18,19].

Preconception care (PCC) focuses on improving women’s health, including lifestyle behaviors, before pregnancy and plays an essential role in encouraging healthy lifestyle behaviors in preparation for pregnancy. Therefore, it reduces the risk of adverse pregnancy outcomes and improves health outcomes in mothers and their children now and later in life [20,21]. PCC is usually delivered face-to-face, for example, at midwifery practices or hospitals. However, web-based PCC has been gaining popularity, which are delivered through video consultations or even combined as blended care [22].

The low uptake of PCC by the general population in the Netherlands is associated with women’s perceived absence of risks and lack of awareness of PCC [23]. The delivery of PCC for women with a vulnerable health status faces even more obstacles, as these women are more difficult to reach and more difficult to motivate to engage in PCC [24]. These obstacles may lead to an ethically unjustifiable inequality in the health outcomes and life prospects of mothers and children from different socioeconomic backgrounds [24].

To encourage pregnancy preparation, our research group developed the web-based mobile health (mHealth) platform *Smarter Pregnancy* [19], an internet-based, tailored coaching platform that supports women who wish to become pregnant (and possibly their partners) to adopt healthy lifestyle behaviors (such as folic acid supplement use, adequate intake of vegetables and fruits, and cessation of smoking and alcohol consumption) before and during pregnancy. Previous research on the effectiveness of *Smarter Pregnancy* has shown that these healthy behaviors increase by at least 30% and that the chance of an ongoing pregnancy after fertility treatment increases by more than 50% [19,25,26]. Furthermore, *Smarter Pregnancy* has proven to be effective and highly valued by women from deprived neighborhoods [27]. This shows the potential of tailor-made mHealth for women with a vulnerable health status and underlines the importance of customizing an intervention that aims to overcome the obstacles associated with reaching and motivating women with a vulnerable health status to engage in PCC.

Changing behavior and lifestyle habits is challenging for all but even more so for women with a low SES, as they often endure stressful situations and deprived circumstances [28,29]. Therefore, it is advisable to offer this group more support in changing their behavior, which also follows the demands of social justice [30]. One way to support behavioral change is through *nudging*. Nudges are a class of interventions that change people’s choice behavior by influencing their incentives, thereby stimulating beneficial, healthy behaviors that individuals themselves value [31]. This could be, for instance, offering fruit instead of chocolate bars at checkout counters to increase fruit consumption and lower refined sugar intake. Previous research has shown that nudging is a promising intervention to encourage the improvement of healthy eating behaviors [32]. Another example of nudging is loyalty programs, in which people can gather rewards by making healthy choices. Nudging via a smartphone app, especially designed for women with a vulnerable health status, may be very suitable to motivate them to engage in PCC due to the current wide availability of smartphones, as well as among women with a vulnerable health status.

### Hypothesis

We hypothesized that nudging via the app *Pregnant Faster* is a feasible way to encourage pregnancy preparation and increase PCC uptake in women with an SES-related vulnerable health status. We expect that this will eventually lead to improved maternal health and pregnancy outcomes as well as improved health of the offspring in early and later life.

### Aims

In this paper, we aimed to describe in detail the cocreation design process of the mHealth app *Pregnant Faster*, a loyalty program embedded in an app, based on the tailored mHealth lifestyle coaching platform *Smarter Pregnancy.* Furthermore, we aimed to develop a cohort study protocol to test the feasibility of *Pregnant Faster*, comprising overall user satisfaction; the number of booked and visited PCC consultations; and the course of practical conduction with regard to the inclusion process, reward allocation, and finalization. The general goal of *Pregnant Faster* is to encourage women with a vulnerable health status, in an ethically justified way, to adequately prepare for pregnancy by visiting a PCC consultation.

If the results of this study indicate that *Pregnant Faster* is appreciated by the participants and stimulates the uptake of PCC, we aim to continue this proposed study with an updated version of *Pregnant Faster* and an extended cohort, to establish the effectiveness of increasing the uptake of PCC in women with an SES-related vulnerable health status.

Our ultimate goal is to contribute to the reduction of inequalities in the health of women before and during pregnancy by (1) creating awareness regarding women’s own influence on the course of their pregnancy and an increased uptake of PCC, (2) reducing perinatal morbidity and mortality, and (3) improving the long-term physical and mental health of mothers and their children.

## Methods

### The Cocreation Process

#### Preparation

The preparation of the design process of *Pregnant Faster* can be subsumed under 3 pillars. First, we have developed an ethical framework to assess the ethical justifiability of developing a loyalty program to stimulate PCC uptake among women with a vulnerable health status. An ethical framework can be viewed as a guideline that offers guidance on the moral permissibility of an intervention and provides suggestions on how to avoid ethical pitfalls, such as exposing susceptible participants to stigmatization based on their SES. This framework was developed by performing a literature search to identify records broadly relevant to the subject of using nudges to stimulate healthy lifestyle behaviors and extracting ethical dilemmas and pitfalls from these records. On the basis of these extracted dilemmas and pitfalls, criteria were set up to which an incentive-based intervention encouraging pregnancy preparation in susceptible women must comply to be morally justifiable. These criteria were subdivided under the 4 ethical principles of Beauchamp and Childress [33]: (1) respect for autonomy, (2) beneficence, (3) nonmaleficence, and (4) justice. By addressing all 4 principles, an attempt was made to address as many ethical pitfalls as possible without overlooking any major aspects. This *principlist* approach is ideally suited for the topic of nudging women with an SES-related vulnerable health status because it allows for balancing between the duty to improve their and their children’s health and well-being and the duty to respect them and treat them as free and equal persons.

Second, we conducted semistructured interviews with 15 women from the target group, which allowed us to gain insight into how they regard loyalty programs; which type of loyalty program they prefer; and which rewards are considered most legitimate, attractive, and effective [34]. The interviews were analyzed using a framework approach and thematic content analyses of five themes: (1) “usefulness of an app as an integral information source,” (2) “permissibility and effects of offering rewards,” (3) “preferences regarding content,” (4) “preferences regarding the type of rewards and system of allocation,” and (5) “barriers.” Involving the target group in the design of the app, thereby respecting their autonomy and preferences, is an imperative criterion of the ethical framework.

Third, we based the lifestyle-related content of the app on the tailored mHealth lifestyle coaching platform *Smarter Pregnancy. Smarter Pregnancy* has previously proven to be effective in ameliorating preconceptional health and lifestyle behaviors and is based on over 30 years of research and the expertise of this research group regarding the influence of nutrition and lifestyle on reproduction and pregnancy course and outcome [25]. The main focus of *Smarter Pregnancy* lies in the amelioration of nutrition, including folic acid supplement use, and supporting healthy lifestyle behaviors such as reaching a healthy weight, smoking and alcohol cessation, and sufficient physical activity.

The knowledge gained through these 3 pillars was combined into a first design of the app *Pregnant Faster*. The choice to develop this loyalty program as a nudge was based on the fact that women are known to wish for a healthy baby when they want to become pregnant [23,35]. Thus, the definition of nudging is that a nudge always aims to help the *nudgee* reach a goal they themselves wish for and value [31]. In addition, a nudge may not harm the nudgee. This description complies with the aforementioned biomedical ethical principles.

#### Iterative Cocreation

Subsequently, we conducted a strategic work session with professionals in this field (5 midwives, 2 gynecologists, and 2 general practitioners) in which we discussed our findings regarding moral permissibility, the wishes and preferences of the target group, and the first design of the app. The professionals asked to participate were known to practice in low-income areas, providing them with experience in caring for the target group of women with a vulnerable health status. The strategic work session was led by an external communication bureau specialized in transforming these types of sessions and the yielded insights into practical reports. These insights were then implemented in the app, leading to the design of a new and improved version of the app, adhering to the ethical framework. Through an iterative process (Figure 2), adjusted versions of the app were discussed by the communication bureau multiple times with 10 women in the target group who had previously participated in the interview study [34] and the aforementioned professionals, until all were satisfied with the design of the app and the app was considered morally permissible. The resulting app-based nudge *Pregnant Faster* can be viewed as an *umbrella* or a *macro-level* nudge, containing multiple *micro-level nudges*.

**Figure 2 figure2:**
[figure not shown]
Overview of the intervention. MAUQ: mHealth App Usability Questionnaire; PCC: preconception care; SES: socioeconomic status.

### Cohort Study Protocol

#### Overview

This study was set up as an open cohort to reflect the real-life situation, and it aims to assess the feasibility of the mHealth app–based nudge that stimulates PCC uptake in women with an SES-related vulnerable health status.

After inclusion (T0), the women start the intervention, consisting of using the app daily. The total duration of the intervention will be 4 weeks per participant, as we deemed a short period of active engagement more feasible than a longer period and did not expect additional engagement in pregnancy preparation or PCC consultations after 4 weeks of using the app.

After the intervention (T1), participants fill out the “mHealth App Usability Questionnaire” (MAUQ), assessing the app, as well as partake in an interview in which they may state their opinions regarding the content of the app and how they rate their experience. At T1, we will assess the uptake of PCC as well (Figure 3). The results of this study will provide further insights to enhance the final design of the nudge and the app and can be viewed as another round in the iterative process, implementing the opinions and experiences of the target group into the final design. After this proposed cohort study, we aimed to update *Pregnant Faster* and plan to establish its effectiveness in a cohort of 400 women. Originally, the sample size of 400 was based on a power calculation for a randomized controlled trial with 2 groups using the app: one with and one without the allocation of rewards. However, the choice was made to convert the planned controlled trial to a cohort study due to the nature of this intervention and the possible disappointment women would feel if they would be randomized in a nonreward group, which could lead to disengagement and biased outcomes.

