#### Outcome Measures

The main objective of this study design is to establish the feasibility of the app *Pregnant Faster* as a nudge that encourages pregnancy preparation by stimulating the uptake of PCC. Feasibility in this study pertains to overall user satisfaction, the number of booked and visited PCC consultations, and the course of practical conduction with regard to the inclusion process, reward allocation, and finalization. The outcome will be assessed in multiple ways: (1) through the number of women who registered for this study, which indicates the effectiveness of the methods used to reach women; (2) the number of women eligible to participate, which indicates the effectiveness of these methods in reaching the target group; (3) the number of participants who were included and the number who actually started the intervention, which may reveal possible barriers between inclusion and conduction; (4) the number of participants completing the intervention, which offers information on how engaging the app is; and (5) the frequency with which certain rewards are chosen that indicates which rewards are deemed the most desirable and motivating. Furthermore, the usability of the app will be assessed using the MAUQ, a validated 18-item questionnaire on user satisfaction, information arrangement, and usefulness based on a 7-point Likert scale (strongly disagree, disagree, somewhat disagree, neither agree nor disagree, somewhat agree, agree, and strongly agree) as presented in Multimedia Appendix 1 [38].

To further investigate how participants have experienced using the app, the first 10 participants will be interviewed in a semistructured manner to explore the answers they give on questions such as how often they opened the app and if this was according to how often they would have liked to open the app. A topic list and additional information on this interview is present in Multimedia Appendix 2. This topic list and participants’ answers will be converted into a questionnaire offered to the remaining 30 participants. To include the first 10 participants in this questionnaire, the first author will fill in the questionnaire based on the participants’ answers in the interview. The MAUQ and the interview or additional questionnaire will be offered 4 weeks after a participant has started the intervention (T1).

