The number of PCC consultation requests and confirmed visits will be registered during the study period and in the aforementioned questionnaires, women will be asked why they registered (or did not register) for a PCC consultation and if they changed their lifestyle behaviors due to using the app. Descriptive statistics will be used for these outcomes, and the results will be reported in a narrative and tabular form.

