**Figure 5 figure5:**
[figure not shown]
The transtheoretical model of health behavior change by Prochaska and DiClemente [36]. (1) Precontemplation: unaware of the need for change and unwilling to change. (2) Contemplation: aware of the problem but not yet committed to change. (3) Preparation: believes change is good, intent on taking action, and planning to start. (4) Action: actively changing behavior or creating new habits. (5) Maintenance: behavior has changed, committed, and resolved; must be aware of the possibility of relapse. (6) Relapse: relapsing into old behavior; may skip precontemplation in the next cycle.

Participants in any stage of change may choose to register for a PCC consultation as the reward is high and the required action (filling in their phone number) is relatively small. This was decided consciously to meet the main objective of *Pregnant Faster*, stimulating pregnancy preparation by visiting a PCC consultation provided by a health care provider. These face-to-face consultations allow health care providers to directly apply motivational conversation techniques [43] and actively match the participant’s current stage of change on the topics that are most relevant for them, for instance, smoking cessation, an unhealthy diet, or a sedentary lifestyle. Having an engaging, live conversation in which the participant can ask questions and feels heard and supported may be the greatest encouragement or nudge to engage in adequate pregnancy preparation and make healthy choices. Furthermore, a live consultation allows for relevant referrals (eg, for smoking cessation) without relying on the participant to take the first step.

This intervention is completed after 4 weeks. If women still have coins left by the end of the intervention, they will be able to exchange these for rewards within 2 weeks after the completion date or 2 weeks after their PCC consultation. The app and timeline will continue to be available for participants, so they can access its information and register for a PCC consultation whenever they please, but they will no longer be able to earn or spend coins by using the app.

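### The window for counting visited PCC consultations is inconsistent (T1, an undefined study period, or after completion), so the visited count may be cut short or rest on unequal follow-up

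*Protocol article*

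**What the plan says.** Feasibility includes "the number of booked and visited PCC consultations" (Outcome Measures; the Aims say the same), so bookings and visits are both outcomes. On when they are counted, three places differ.

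- **Cohort Study Protocol, Overview.** "The total duration of the intervention will be 4 weeks per participant", and then: "At T1, we will assess the uptake of PCC as well". Part of the reason for the short period is that the authors "did not expect additional engagement in pregnancy preparation or PCC consultations after 4 weeks of using the app". Outcome Measures dates T1 at 4 weeks after the participant starts.
- **Outcome Measures.** "The number of PCC consultation requests and confirmed visits will be registered during the study period". The study period is not defined, and this sentence does not mention T1.
- **The App Design, text after Figure 5.** For women with coins left at the end, "they will be able to exchange these for rewards within 2 weeks after the completion date or 2 weeks after their PCC consultation". The app stays available and registration for a consultation stays open without an end date, "but they will no longer be able to earn or spend coins by using the app".

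The App Design also separates the request from the visit: 25 coins come at sign-up, and 75 more once the visit is confirmed.

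**The concern.** A woman may ask for a consultation on any of the 28 days, and the visit follows after some wait. The reward rules leave room for that visit to fall after the 4 weeks, but the Overview reads uptake at 4 weeks on the premise that nothing follows. Under a strict T1 reading, a woman who books late and attends on, say, day 35 is recorded as booked but not visited. The gap between requests and visits then looks like non-attendance when part of it is only waiting time.

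The visited count matters because attending a consultation is the behaviour the app is meant to produce. The Abstract and the Aims also make continuation to a further 400 women depend on uptake as well as on user satisfaction. A count that changes with an unstated window is a weak basis for that decision, even in a descriptive pilot.

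**Working it through.** **Inputs from the protocol article.** Intervention of 4 weeks = 28 days, with T1 at day 28; 40 participants; exchange of leftover coins until 2 weeks (14 days) after completion or after the consultation; descriptive analysis only.

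**Inputs not given.** The wait from request to visit, the distribution of requests over the 28 days, and eventual uptake. Every value used for them below is an assumption. The article states no uptake figure that could be reproduced. Its one checkable number, 10% of 400 = 40, is correct but does not bear on this point.

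**Step 1: does the exchange rule provide for visits after T1?** The completion-based deadline is day 28 + 14 = 42. For a visit on day d, the consultation-based deadline is day d + 14. This is later than day 42 only if d > 28. For any visit up to T1 the second deadline gives no extra time, so it has an effect only for a consultation held after T1. The reward rules therefore provide for visits that a T1 count does not cover.

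**Step 2: share of visits seen at T1 under a strict reading.** With requests spread evenly over 28 days and a fixed wait of w days, the share is (28 − w)/28. With front-loaded requests (exponential with a 7-day half-life, truncated at day 28), it is (1 − 2^(−(28 − w)/7)) / (1 − 2^(−4)).

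| Assumed wait | Even requests | Front-loaded requests |
|---|---|---|
| 7 days | 21/28 = 75% | 0.875/0.9375 = 93% |
| 14 days | 14/28 = 50% | 0.75/0.9375 = 80% |
| 21 days | 7/28 = 25% | 0.5/0.9375 = 53% |

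**Step 3: effect on the visited count.** Let p be the share of the 40 women who eventually attend, and q the share of those visits held after T1. The expected count at T1 is 40 × p × (1 − q), and the bias in the visited proportion is −p × q.

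| p (eventual visits) | q = 0 | q = 0.25 | q = 0.50 |
|---|---|---|---|
| 0.20 (8) | 8, no bias | 6, −5 points | 4, −10 points |
| 0.30 (12) | 12, no bias | 9, −7.5 points | 6, −15 points |
| 0.50 (20) | 20, no bias | 15, −12.5 points | 10, −25 points |

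With even requests, q = 0.25 and 0.50 correspond to waits of 7 and 14 days. A request made by day 28 is counted as booked in every cell; only the visited count moves.

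**Step 4: the other reading.** Suppose the study period is calendar time that closes at the last participant's T1, and enrolment lasts R weeks (R is not stated). The first enrollee is then observed for R + 4 weeks and the last for 4 weeks. Late visits are caught for early enrollees and missed for the last ones, so the 40 women share no common window.

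**The case against.** A reader might infer that the plan itself expects consultations after week 4 and knowingly leaves them out, so that reported uptake must be too low. The documents do not support that. The Overview says that none were expected; The App Design only makes room for them. Nor is it established that late visits are lost. Outcome Measures does not limit registration to T1, and a deadline tied to the consultation requires the team to know of visits after completion. Bookings are a separate outcome, so a woman with a pending visit is not lost from the uptake picture.

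A reader might also infer that the 75 coins lapse at week 4 and that late bookers lose the incentive to attend. No such rule is stated. The restriction concerns coins earned or spent through use of the app, while these coins follow a confirmed visit. The wording is unclear, but it is not a stated loss.

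Further, every size above rests on assumed waits, and with short waits the loss approaches zero. The study is a single-arm descriptive pilot of 40 women with no numerical uptake threshold. An article may also leave the exact window to the full protocol.

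These points limit the claim to a conditional one, but they do not remove the conflict. The article does more than omit the window: it describes it in ways that do not agree. The broader sentence in Outcome Measures does not settle the matter either, because its study period is undefined and one natural reading gives unequal follow-up.

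**Conclusion.** The point holds as an inconsistency in the window for visited consultations, with consequences that depend on how it is resolved. Under a strict T1 count, the visited count can only be too low, by p × q. Under calendar-time counting, follow-up differs between early and late enrollees. If all visits were followed to a common later date, neither problem would arise, but the article does not say that this is done.

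The documents fix the direction under the strict reading, not the size. The 75% and 50% captured at waits of 1 and 2 weeks assume even requests and a fixed wait; front-loaded requests give 93% and 80%. A certain downward bias in overall uptake is not shown. The correction is worth making because it is cheap and settles a count that informs the decision to continue.

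**What to change.** Define one window per participant. Count requests from the start of the intervention to day 28. Count confirmed visits arising from those requests up to one fixed later cut-off, the same for everyone. The sponsor should choose that cut-off from the waits seen in the participating practices. Because women already pregnant at entry are eligible, the choice should also consider how late a visit can still sensibly count as PCC.

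Report booked, visited and still-pending consultations separately, with the visit count at T1 as a secondary figure. Pending visits then cannot be mistaken for non-attendance.

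Reconcile the Overview, Outcome Measures and The App Design on this window, and state whether coins for a visit held after week 4 are still credited.

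The cost is a short wait after the last T1 before the visit count is closed. Visits are already confirmed for the award of coins, so no new procedure should be needed, only continued recording to the cut-off.
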